## Abstract

**Introduction:** Recent studies have shown that symptoms of psychiatric illness, functionality, and cognitive function improve with exercise. The aim of this study will be to investigate whether the implementation of an individualized exercise program will improve the functional status of patients with bipolar disorder (BD).

**Methods:** This longitudinal, interventional, randomized, controlled, simple-blind clinical trial will include 80 patients aged 18–65 years, all of them with BD diagnosis. Patients will be randomly assigned to a physical exercise intervention + Treatment-As-Usual (TAU) group and a non-intervention + TAU group. Patients will be assessed by an extensive battery of clinical tests, physical parameters (e.g., brain structure changes measured by optical coherence tomography, cardiorespiratory fitness) and biological parameters (inflammation, oxidative stress and neurotrophic factors) at baseline, after a 4-month intervention period, and 6-month follow-up.

**Discussion:** This is an innovative study aimed at gaining a deeper understanding of the physiopathology of BD and determining whether the prognosis and evolution of the disease can be improved through modifiable areas of the patient's lifestyle.

**Clinical Trial Registration:** NCT04400630. NCT clinicaltrials.gov. Date of registration in primary registry 22 May 2020. clinicaltrials.gov.

## Introduction

Bipolar disorder (BD) is a mood disorder affecting about 400 million people worldwide (1). This psychiatric disease is a chronic disorder associated with cognitive dysfunction, increased mortality and intensive use of healthcare services (2, 3). The management of BD involves a combination of pharmacological therapies and psychosocial interventions including, but not limited to, cognitive-behavioral therapy, functional remediation, family psychoeducation, social skills training and protected employment (4). Despite therapies, the risk of recurrence is high, and patients often do not recover completely. Failure of current therapies to induce the remission of BD symptoms has led researchers to focus their efforts on developing more effective treatments (5).

In the search for new therapeutic strategies, physical exercise has been found to play a relevant role in the treatment of psychiatric disorders (6). Thus, physical exercise is not only effective in improving cardiorespiratory function, physical status, and metabolic syndrome (common comorbidities in BD), but it has also proven to reduce depressive symptoms and suicidal ideation (7).

Several studies have documented that moderate-to-vigorous physical exercise intensity programs influence the progression of mood disorders (8) and also improves cognitive performance and functionality in patients with schizophrenia (9). Concerning these results, at a biological level, physical exercise increases levels of neurotransmitters, cortisol, beta-endorphins, and neurotrophic factors such as BDNF (brain-derived neurotrophic factor) (8). It has been shown that serum levels of BDNF are reduced in persons with BD (10, 11) and major depressive disorder (12, 13). This neurotrophic factor plays a key role in neurological development, adult brain plasticity, neuron survival and differentiation, neuronal function, repair mechanisms of brain plasticity, and stimulates neurogenesis after the activation of its TrkB receptor (9). This receptor has two isoforms: a functional isoform with TrKB-FL activity, and a *truncated* isoform without TrkB-T activity (14). Elevated TrkB-T levels may induce neuronal death by the inhibition of the functional TrkB-FL isoform. In this line, patients with schizophrenia have been reported to exhibit increased levels of the *truncated* isoform in the prefrontal cortex (15). Indeed, TrkB-T levels in peripheral blood are more strongly associated with the early stages of psychosis than BDNF levels (14).

Physical exercise also modulates the body's response to stress and optimizes its antioxidant and anti-inflammatory capacity. Since BD patients have been reported to have an inflammatory state at the peripheral and central nervous system (16), the anti-inflammatory effects of physical exercise could play a relevant role in the physiopathology of the disease (17).

Interaction between the mechanisms described above explains how physical exercise can reduce symptoms of mood disorders and recurrence rates, thereby improving the quality of life and functionality of patients (18).

In line with the goal of better understanding the physiopathology of psychiatric diseases, brain imaging has been used for 15 years to assess brain alterations associated with these disorders. In BD patients, gray matter shrinks in the hippocampus, the fusiform gyrus, and the temporal lobe. The severity of brain alterations are related to symptoms and the number of episodes experienced by the patient (19). Patients with schizophrenia also show a loss of brain volume even since the first psychotic episode and in prodromal stages (20). Several authors have postulated that the retina could be an accessible marker of the structural and/or functional integrity of the brain (21–23). This hypothesis is grounded on the fact that the retina develops from the same embryonic layer as the brain. The retina and the brain are connected via the optic nerve, which would allow direct observation of the brain (22). Retinal alterations might be concomitant to the inflammatory and neurodegenerative processes and structural central nervous system alterations associated with BD (24). The retina is considered to be a part of the brain and contains several layers of neurons that are connected by synopses. The retinal nerve fiber layer (RNFL) is composed of unmyelinated axons of nodal cells. The ganglion cell complex contains the three innermost layers of the retina and comprises the retinal nerve fiber layer, the ganglion cell-inner layer, and the inner plexiform layer. Optical coherence tomography (OCT) is a non-invasive, no-contact, rapid imaging technique without known side effects that provides high-resolution and cross-sectional images of the retina, and measures RNFL (25). Some studies have reported OCT abnormalities such as retinal layer thinning (also in RNFL) associated with different neurological disorders with degenerative changes, including Parkinson's disease (26), Alzheimer's disease (27), and multiple sclerosis (28). Connecting with the growing interest in this technique for the diagnosis of neurodegenerative diseases, a recent study revealed that OCT demonstrated a thinning of retinal layers in patients with schizophrenia and schizoaffective disorder, as compared to a group of healthy individuals (29).

Previous studies have shown that physical exercise is an effective antidepressant intervention (30), but no studies have been able to provide a comprehensive overview of the mechanisms that produce these benefits in terms of patient prognosis. This fact led us to conduct a longitudinal comparative study to assess the impact on FunctIonality and Neurocognition of an individualized moderate-to-vigorous physical EXercise Training in a population of patients with BD (FINEXT-BD study).

We hypothesize that this intervention will improve the functional status of patients and this improvement will be reflected in physical and biological parameters. Thus, the primary aim of this study will be to investigate whether the implementation of an individualized moderate-to-vigorous physical exercise intensity program as adjuvant therapy to standard drug therapy will improve the functional status of patients with BD, as compared to a group of patients with BD without intervention. The specific secondary objectives of the study will be to: (1) investigate whether the implementation of this exercise program modifies the cognition, the clinical symptoms and incidence of comorbidities; (2) investigate whether the implementation of this exercise program induces changes in the levels of oxidative and inflammatory parameters and these changes correlate with the evolution of clinical symptoms; (3) whether BDNF and TRkB-FL/TRkB-T ratio are associated with the evolution of the patient's functional and neurocognitive capacity, and (4) whether changes in the thickness of retinal layers as measured by OCT correlate with the functionality and neurocognitive function of BD patients.

## Methods and Analysis

### Design

The FINEXT-BD study is a longitudinal, interventional, randomized, controlled, simple-blind trial conducted at the University Hospital of Araba in a cohort of BD patients divided into two groups: (1) physical exercise intervention + Treatment As Usual (TAU) (intervention group) and (2) patients with no intervention + TAU (TAU group). In addition, a gender-, race-, and age-matched healthy control group will be added to compare biological and physical parameters and the functional and neuropsychological status, with the cohort of BD patients.

Treatment As Usual will be defined as the prescribed pharmaceutical treatment by the clinician at the dose indicated for euthymic patients, with regular monthly visits that can be increased to weekly or biweekly sessions in the presence of prodromal symptoms or relapse.

#### Randomization and Blinding

FINEXT-BD patients will be randomly assigned to the groups (1:1) using Random Allocation Software version 1.0.0 software. Study evaluators will be blinded to the treatment branch. Patients will continue their usual treatment and will be treated by their reference psychiatrist, who will be informed of patient's participation in the interventionist program and will make sure that the appropriate clinical treatment is administered.

The flow diagram of the study can be seen in Figure 1.

**Figure 1 F1:**
[figure not shown]
FINEXT-BD study procedure.

### Participants

#### Patients

The sample of patients with BD will be recruited by trained and experienced psychiatrists from patients treated in the Inpatient and Outpatient Unit of Psychiatry of the University Hospital of Alava.

Inclusion criteria will be:

Diagnosis of BD according to the Diagnostic and Statistical Manual of Mental Disorders, Fifth Edition (DSM-5) (31), diagnosis based on semi-structured SCID-P interview (32). The study will involve patients with first-episode or multiple episodes of mania. Patients will be required to be euthymic at baseline, defined as no current diagnosis of an episode of mania, hypomania, or depression. Relapse during follow-up or presence of subsyndromal symptoms at any moment will not be exclusion criteria.Age between 18 and 65 years.Speak Spanish correctly.

Exclusion criteria will be:

Intellectual disability (assessed by DSM-V).History of cranial trauma with loss of consciousness.Physical diseases that cause mental health problems.Pervasive developmental disorders.Pregnancy or breastfeeding.Be classified as “physically active” according to the Global Physical Activity Questionnaire (GPAQ) (33).The presence of a severe or uncontrolled cardiovascular risk factor such as unstable coronary artery disease, uncontrolled hypertension, malignant ventricular arrhythmia, atrial fibrillation, exercise-induced ischemia, and ventricular failure during exercise.Other significant medical conditions including, but not limited to chronic or recurrent respiratory, gastrointestinal, neuromuscular, or any musculoskeletal problems interfering with exercise.The presence of inflammatory diseases.Consumption of anti-inflammatory drugs during the week prior to blood extraction.

#### Controls

Controls will be recruited from friends of patients and healthcare personnel. If the established N is not reached, informative posters will be placed in different hospitals. In such case, posters will be sent to the CEIC for evaluation.

The inclusion criteria will be:

Age between 18 and 65 years.Speak Spanish correctly.

The exclusion criteria will be:

Intellectual disability (assessed by DSM-V).History of cranial trauma with loss of consciousness.Physical diseases that causes mental health problems.Pervasive developmental disorders.Pregnancy or breastfeeding.Consumption of anti-inflammatory drugs during the week prior to blood extractionThe presence of inflammatory diseases.History of psychiatric episodes among first-degree relatives.

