#### Sociodemographic Variables

Data on sociodemographic variables (age, sex, educational level, socioeconomic level, employment status, family history of psychiatric disorders, number of relapses, years of disease evolution, and number of manic episodes) will be collected at baseline.

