### Statistical Analysis

A general descriptive analysis of the sample will be performed to assess baseline homogeneity. The normality of quantitative variables will be assessed by the Kolmogorov-Smirnov test and results will be expressed as means and standard deviation or as median values and interquartile range in the case of non-normal distribution. Qualitative variables will be expressed as frequencies and percentages.

To respond to the main aim, analysis of covariance (ANCOVA) will be used to assess the improvement in functionality. The same test will be used to analyze the difference between the groups.

At baseline, an analysis of variance (ANOVA) will be performed to confirm that there is no difference between patient groups, but there is a difference with the control group.

Student's *t*-test for related samples will be used to assess changes after the physical exercise program between intervention patient groups, among normally distributed variables. Changes in the variables studied across the three visits will be assessed by an analysis of repeated measurements. The analysis of repeated measurements will be used to assess the evolution of the variables studied during the three visits. Non-normally distributed variables will be assessed using Wilcoxon test. Univariate and multivariate regression analysis will be performed to determine whether statistically significant differences are associated with the evolution of the functionality and clinical and cognitive symptoms. All statistical analyses were carried out using SPSS v23.0 and R v3.5.0 statistical software, with the significance level set at *p* < 0.05.

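### The baseline comparison of bipolar patients with healthy controls is matched on gender, race and age only and tested without adjustment, so a functional or cognitive difference may partly reflect education

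*Protocol article*

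**What the plan says.** All references are to the protocol article.

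- **Purpose and matching (Design).** The article states that "a gender-, race-, and age-matched healthy control group will be added to compare biological and physical parameters and the functional and neuropsychological status". No other matching factor is named.
- **Source (Controls).** "Controls will be recruited from friends of patients and healthcare personnel". Posters in hospitals are the fallback. The control eligibility criteria do not mention education or employment.
- **Analysis (Statistical Analysis).** "At baseline, an analysis of variance (ANOVA) will be performed to confirm that there is no difference between patient groups". The same test is also meant to establish that patients differ from controls. No covariates are named. Adjustment appears elsewhere, for the primary question: "To respond to the main aim, analysis of covariance (ANCOVA) will be used to assess the improvement in functionality".
- **Data (Sociodemographic Variables).** The baseline list includes "educational level, socioeconomic level, employment status". No section uses these variables to match, restrict or adjust the comparison with controls.
- **Visits (Assessments).** Controls are seen at baseline only.

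**The concern.** Matching on three demographic factors removes confounding by those factors and no others. Education is the obvious one left. The neuropsychological battery (Stroop, TAVEC verbal learning, Wisconsin card sorting) can be expected to vary with schooling, and one possible source of controls is hospital staff, whose schooling may differ from that of patients recruited in inpatient and outpatient psychiatry. Employment raises a related question, because FAST scores occupational functioning as one of its six areas, and staff are in work.

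An unadjusted ANOVA cannot separate the effect of the disease from the effect of where controls were found. The test is also framed as confirming that a difference exists, so an inflated difference would look like the expected result and prompt no further check. At stake is the interpretation of the patient-versus-control results on cognition and functioning. The effect of exercise is not at stake.

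**Working it through.** The plan gives no figure on this point, so there is none to reproduce. The check has two parts.

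**1. The text.** Four statements have to be read together: matching on gender, race and age (Design); recruitment from friends of patients and healthcare personnel (Controls); an ANOVA without covariates (Statistical Analysis); and educational level on the baseline list (Sociodemographic Variables). The ANCOVA is tied to the main aim. The regressions at the end of Statistical Analysis concern the evolution of functionality and symptoms. Neither reaches the comparison with controls. Since controls have no later visit, the baseline contrast is the only direct comparison with them.

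**2. Illustration of size.** The inputs, and where they come from:

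- Patients: 40 + 40 = 80 (Sample Size).
- Controls: no number is given, so 20, 40 and 80 are assumed.
- Education gap between controls and patients: 0.5 to 1.0 SD, assumed.
- Correlation of education with a test score: 0.3 to 0.5, assumed.
- True disease effect: set to zero, to isolate the bias.

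Spurious difference in SD units: d = gap × correlation. The low end is 0.5 × 0.3 = 0.15 and the high end is 1.0 × 0.5 = 0.50. An intermediate value of 0.30 is also shown.

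The planned test compares three groups (two patient arms and controls). If the two patient arms have equal means and controls differ by d, the noncentrality of the F test is

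λ = d² × 80 × n_c / (80 + n_c), with 2 and (80 + n_c − 3) degrees of freedom.

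For n_c = 40: d = 0.15 gives λ = 0.0225 × 3200 / 120 = 0.60, and d = 0.50 gives λ = 0.25 × 3200 / 120 = 6.67.

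Chance of p < 0.05 on one test with no disease effect:

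| Controls (assumed) | d = 0.15 | d = 0.30 | d = 0.50 |
|---|---|---|---|
| 20 | 7.7% | 16.9% | 40.4% |
| 40 | 9.7% | 25.8% | 62.1% |
| 80 | 12.2% | 37.2% | 80.8% |

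The nominal rate is 5%. A two-group t-test that pools the patients would give higher rates (12.0% to 72.6% with 40 controls), but it is not the test the article implies.

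The assumptions drive the result. A different set, with shares of higher education differing by 20 to 60 percentage points and education shifting a score by 0.3 to 0.8 SD, gives a bias of 0.2 × 0.3 = 0.06 to 0.6 × 0.8 = 0.48 SD. The three-group ANOVA then rejects in about 6% to 58% of studies with 40 controls. At the low end the problem is negligible, and at the high end it is serious.

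**The case against.** The case on the other side has several parts.

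- **The comparison is peripheral.** The primary aim and the four listed secondary objectives contain no patient-versus-healthy-control contrast. This is right, and it limits the importance of the point. A reader might infer that the trial's main result is compromised. It is not, because exercise and treatment as usual are compared under randomisation and healthy controls play no part in that.
- **An article may leave covariates to the full plan.** This is partly right. But the article does state the matching factors, the source and the test. Followed as written, that method leaves education uncontrolled, so the point concerns a stated choice and not mere lack of detail.
- **The recruitment sentence can be read two ways.** It can mean staff themselves, or friends of patients and friends of staff. A reader might infer that controls are employed by definition. The second reading does not support that, and even under the first the share of staff is not given and friends of patients may share the patients' background. Under either reading, education remains unmatched and unadjusted.
- **The size rests on assumptions.** This stands. In addition, the Introduction starts from BD being associated with cognitive dysfunction, so the realistic risk is an inflated true difference more than a false one. A reader might also infer a large bias on FAST: if the occupational area held 3 to 5 of the 24 items at up to 3 points each, it would carry 9 to 15 of the 72 points. That is a ceiling on an assumed item count, reached only if every patient scored worst and every control best. The article gives no item count per area, and the figure is no estimate of bias.
- **Adjustment has its own cost.** BD can itself shorten schooling, so adjusting for education may remove part of the disease effect. This stands, and it argues for showing both results, not for replacing one by the other. It applies more strongly to employment, which may be a consequence of BD and is part of what FAST measures.
- **The article does not claim causal attribution.** It speaks of comparing and of a difference. This is correct, so the advice on attribution is a safeguard for reporting and does not correct a claim the article makes.

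**Conclusion.** The point holds in a limited form. The baseline comparison of BD patients with healthy controls on functional and neuropsychological status is ancillary, matched on three factors and tested without adjustment, while educational level is planned for collection and unused here. A difference may therefore partly reflect education.

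The bias cannot be derived from the documents, which give neither the number of controls, nor the share of staff, nor an education gap. Under an assumed spurious difference of 0.15 to 0.50 SD and no disease effect, the planned three-group ANOVA would reject in about 10% to 62% of studies with 40 controls, 8% to 40% with 20, and 12% to 81% with 80. These figures show what could happen and do not predict what will. A change in the recruitment source or the matching is not required by this point; both are open design preferences.

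**What to change.** In Statistical Analysis, for the neuropsychological and functional comparisons of patients with healthy controls:

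1. Report an ANCOVA adjusted for age, sex and educational level beside the unadjusted ANOVA.
2. State that the unadjusted difference will not be attributed to BD alone.
3. Do not adjust for employment in the main model. Show FAST by area as well as in total, so that the contribution of the occupational area is visible without discarding it.

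Two small clarifications would help: whether controls include healthcare personnel or their friends, and that the baseline sociodemographic variables are recorded for controls as well as patients.

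The cost is a change of analysis wording and one extra summary, using a variable already on the baseline list. The downside is that education adjustment may remove some true disease effect; reporting both results lets the reader see how much the estimate moves.

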### Assessments

Data collection will be based on an assessment protocol for gathering data on sociodemographic, physical, clinical, and biological variables. Patients from the two groups will be evaluated by blind raters at baseline (pre-intervention), after a 4-month intervention period, and 6-month follow-up period. Blood sampling for the analysis of biological parameters will be performed during the same visits. The control group will be evaluated only at baseline.

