## Anticipant Results

This study anticipates that the patients belonging to the intervention group, at the end of the individualized physical exercise program, will show an improvement of their functional capacity, as compared to the TAU group. In addition a decrease in the clinical symptoms of the disease, as well as a better score on the neuropsychological scales is expected. Furthermore, completion of the intervention program will have greatly increased adherence to treatment in these patients. If we confirm our hypothesis, all these improvements will be reflected at the biological substrate level (decrease in oxidative and inflammatory parameters and increase in BDNF) and physical level (changes in retinal structure and anthropometrics) in the post-intervention and follow-up visits, compared to the control group.

Further, this program of physical exercise performed regularly for 16 weeks will provide patients with guidelines to improve their lifestyle and quality of life, which will be reflected in the post-intervention and follow-up visit at 6 months after the end of the intervention program.

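### Patients classed as physically active are excluded but controls have no activity criterion, so the baseline bipolar-versus-control biomarker contrast may partly reflect activity rather than disease

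*Protocol article*

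**What the plan says.** **Purpose of the controls (Design).** The article states that "a gender-, race-, and age-matched healthy control group will be added to compare biological and physical parameters", together with functional and neuropsychological status. Gender, race and age are the only matching factors, and the word healthy is not defined.

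**Patient criteria (Patients).** One exclusion is to "Be classified as “physically active” according to the Global Physical Activity Questionnaire (GPAQ"). Inflammatory disease and recent anti-inflammatory medication are also excluded.

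**Control criteria (Controls).** Inclusion is "Age between 18 and 65 years.Speak Spanish correctly". The exclusions repeat several patient items, including the two on inflammation, and add "History of psychiatric episodes among first-degree relatives". Neither physical activity nor the control's own psychiatric history appears. Controls come from patients' friends and from healthcare staff.

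**Timing (Assessments).** "The control group will be evaluated only at baseline".

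**Analysis (Statistical Analysis).** A baseline ANOVA is meant to confirm that the two patient groups do not differ from each other but do differ from controls. No activity covariate is named.

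**Expectation (Anticipant Results).** Biological and physical improvements are expected "in the post-intervention and follow-up visits, compared to the control group", whereas the functional comparison in the same paragraph is with the TAU group.

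**The concern.** One side of the disease comparison is restricted to inactive people and the other is not. Disease status is therefore tied to activity level by the eligibility rules themselves, over and above any natural difference in activity. Matching on gender, race and age does not undo this, and nor does the named analysis.

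The article supplies the reason this matters. Its Introduction says that exercise raises BDNF and improves antioxidant and anti-inflammatory capacity, and also that people with bipolar disorder have reduced BDNF and an inflammatory state. Selecting inactive patients would push these markers in the same direction as the disease effect the investigators expect to confirm. A positive result could then be read as a disease signature when part of it comes from who was allowed into each group.

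The GPAQ appears only as a patient exclusion. Unless it is also given to controls, the data needed to separate the two explanations may never be collected.

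**Working it through.** **1. The criteria side by side**

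| Item | Patients | Controls |
|---|---|---|
| Physically active on GPAQ | excluded | no criterion |
| Inflammatory disease | excluded | excluded |
| Anti-inflammatory drugs in the week before sampling | excluded | excluded |
| Own psychiatric disorder | bipolar disorder required | no criterion |
| Psychiatric history in first-degree relatives | no criterion | excluded |

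Two important biomarker confounders are handled equally in both groups. Activity is not.

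**2. Possible size of the activity effect**

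The plan gives no figure to reproduce. It does not state the number of controls, the share who are active, or the effect of activity on any marker, so everything here except the 80 patients is assumed.

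Assumptions: all 80 patients are inactive; there are 40 controls, of whom a share *p* are active; active people differ from inactive people by *d* SD; bipolar disorder has no true effect. The two patient groups are pooled and compared with controls by a two-sided 5% t-test, a simplification of the planned ANOVA.

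Spurious difference = *p* × *d*. The rejection rate is the power of the t-test at that difference.

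| *p* | *d* | *p* × *d* | Rejection rate, 80 v 40 |
|---|---|---|---|
| 0.3 | 0.3 | 0.09 | 0.075 |
| 0.3 | 0.5 | 0.15 | 0.12 |
| 0.3 | 0.8 | 0.24 | 0.23 |
| 0.5 | 0.3 | 0.15 | 0.12 |
| 0.5 | 0.5 | 0.25 | 0.25 |
| 0.5 | 0.8 | 0.40 | 0.54 |
| 0.7 | 0.3 | 0.21 | 0.19 |
| 0.7 | 0.5 | 0.35 | 0.43 |
| 0.7 | 0.8 | 0.56 | 0.82 |

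The range is about 8% to 82% against a nominal 5%. Over the same grid it is about 7% to 60% with 20 controls and about 9% to 94% with 80. More controls make the false signal easier to detect; they do not remove it.

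**3. A control's own psychiatric illness**

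Suppose a share *q* of controls have a disorder that carries the full bipolar effect. A true difference *D* is then observed as *D* × (1 − *q*). Take *D* = 0.65, borrowed from the Sample Size section purely for scale:

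- *q* = 0.05: 0.65 × 0.95 = 0.62
- *q* = 0.30: 0.65 × 0.70 = 0.46

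This shrinks the contrast; it does not create one.

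**4. Later visits**

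Assessments gives controls one visit, at baseline. Anticipant Results refers to a control group at the post-intervention and follow-up visits. Healthy controls have no data at those visits, so only the TAU group can be a concurrent comparator there.

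**The case against.** **The contrast is ancillary.** The primary aim compares exercise with TAU in randomised patients, and none of the four listed secondary objectives is a comparison with healthy people. This stands and limits the importance of the point. Even so, the Design section plans the comparison and the Statistical Analysis section tests it.

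**The size is assumed.** This also stands. A range of 8% to 82% shows that the problem could be trivial or large, and does not estimate it.

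**Covariates can be left to an analysis plan.** That is fair as to the adjustment model. It does not cover the eligibility lists, which are set out item by item, or the need to collect the GPAQ in controls.

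**Healthy plainly means free of psychiatric illness.** That is probably the intent, since even relatives' episodes exclude a control. The missing line is therefore a gap in wording, and its effect would mainly be dilution.

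**Stronger readings that a reader might infer, and that the documents do not support:**

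- *Peak oxygen uptake and DXA body composition are confounded too.* Physical Parameters words the exercise test for patients and ties DXA to the same baseline and post-intervention visits. It is not clear that controls have either.
- *Functioning is biased by activity.* The article offers no basis for an activity shift in functioning among healthy people.
- *The cardiovascular and other medical exclusions should be copied to controls.* They read mainly as suitability criteria for an exercise programme that controls do not enter.
- *A follow-up analysis against healthy controls is planned, with assay-batch problems.* Anticipant Results is a loosely worded expectation, the control analysis is placed at baseline, and nothing says that groups or visits are assayed separately.

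**Conclusion.** The point holds in a limited form. As written, the plan selects inactive patients, leaves controls' activity unrestricted, and names no adjustment in the baseline ANOVA. By the article's own account of what exercise does, a bipolar-versus-control difference in BDNF, inflammatory or oxidative markers cannot be attributed to the disease alone.

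The size cannot be derived from the documents. The spurious difference of 0.09 to 0.56 SD, and the rejection rates of about 8% to 82%, rest wholly on the assumed 30-70% active controls, 0.3-0.8 SD shift and 40 controls.

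The randomised exercise-versus-TAU comparison is unaffected. The absent own-psychiatric-history criterion and the conflict over later control comparisons are secondary and need only corrected wording.

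**What to change.** **Main change.** Apply the GPAQ physically-active exclusion to controls. Alternatively, give the GPAQ to every control, including any already enrolled, and adjust the patient-control comparison for it.

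Exclusion is the cleaner choice. With every patient in the inactive class, adjustment by GPAQ class leans on the inactive controls. Under the assumptions above, 40 controls would include between 40 × 0.3 = 12 and 40 × 0.7 = 28 of them.

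**Secondary changes.**

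- Add the control's own current or past psychiatric disorder to the control exclusions, so that the criteria put the word healthy into effect.
- In Anticipant Results, name the TAU group as the comparator at the post-intervention and follow-up visits, consistent with baseline-only assessment of controls.

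**Cost.** An amendment to the control criteria, one questionnaire per control, and possibly slower control recruitment. Nothing changes in the randomised part of the trial.
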